### Sample size

Sample size is based on our main outcome measure, which is estimating the diagnostic accuracy of biomarkers in tear fluid to discriminate between participants with and without neurodegeneration as determined by hippocampal atrophy. The calculation of sample size is based on the width of the 95% confidence intervals of sensitivity and specificity, as well as recent pilot data from our group [16]. To obtain a margin of error of maximally 10% for sensitivity as well as specificity, 97 individuals with neurodegeneration and 97 without neurodegeneration will be required. This calculation is performed using an online calculator (http://statulator.com/SampleSize/ss1P.html), where an expected proportion (sensitivity and specificity) of 50% was used as this yields the largest sample size. The diagnostic accuracy will be based on baseline parameters. To correct for potential dropout during follow-up, we increased the total number of participants to 200. Within these groups, participants will be divided into subgroups based on the clinical diagnosis. We aim to include a 50 participants per clinical diagnosis in order to obtain sufficient data to study secondary outcomes.

### Statistical analysis

All data will be stored in the online database Castor EDC with restricted access [30]. The final data will be exported to IBM SPSS Statistics (IBM, Armonk, NY, USA) for statistical analysis. Data from participants with missing data or data from withdrawn participants will be included in the statistical analysis. Threshold of statistical significance will be assumed equal to p < 0.05.

Receiver operating characteristic (ROC) analyses will be performed to estimate the capability of tear biomarkers to differentiate between individuals with neurodegeneration and those without neurodegeneration as determined by hippocampal atrophy. The area under the curve and diagnostic accuracy measures such as sensitivity, specificity, predictive values and likelihood rations (with the corresponding 95% confidence intervals) will be calculated to assess the discriminative capability of a biomarker. To study the correlation of biomarker levels in tears, blood, CSF and PET will be performed using Pearson or Spearman correlation. Each biomarker will be separately compared across three body fluids, and the Aβ region of interest SUVr from PET. Based on our pilot results, we expect negative correlations between tears and CSF (similar to blood and CSF) [17]. Diagnostic accuracy will also be determined for the combination of tear and retinal biomarkers. Linear scores will be derived from the total area or partial area under the ROC curve. Lastly, we will study the mean change of tear biomarkers over time and how this correlates with disease progression (based on neuropsychological evaluation, imaging and fluid biomarkers) with the use of (generalized) linear mixed models or repeated measures ANOVA. Post hoc analysis will reveal which groups and time points differ significantly from each other.

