## Background

Approximately 57 million people are affected by dementia globally, and due to the ageing of the global population this number is expected to increase to 152 million cases by the year 2050 [1]. Patients with dementia experience memory problems, disorientation and difficulties with performing routine tasks. Alzheimer’s disease (AD) is the most common cause of dementia. AD is associated with the accumulation of senile plaques (deposits of amyloid-beta (Aβ)) and neurofibrillary tangles (deposits of tau protein (NFT)) in the brain [2] as well as brain atrophy in the cerebral cortex and hippocampus. Other pathological processes can be observed in AD patients alongside or caused by the accumulation of Aβ-plaques and NFT, such as inflammation, oxidative damage, and blood-brain barrier dysfunction [3].

Timely diagnosis is important to promote early and optimal management of the disease. Furthermore, this will be essential for future therapies as they may be more effective when started earlier in the disease process. Patients are diagnosed with subjective cognitive decline (SCD), mild cognitive impairment (MCI) or AD dementia based on clinical symptoms, cognition and daily functioning [4–7]. Additionally, the etiology of the disease can be determined with the use of biomarkers. These biomarkers are classified into three categories: Aβ deposition, neurofibrillary tangles and neurodegeneration (ATN) [8]. Cerebral spinal fluid (CSF) analysis or amyloid positron emission tomography (PET) imaging are currently used for biomarker determination [5, 6]. However, these diagnostic tests are invasive, expensive and not widely available, thereby limiting their potential as a front-line screener. Considering the expected increase of people affected by AD, there will be a growing need for non-invasive and cost-effective tools allowing identification of patients in the earlier phases of the disease [1].

In this study, we propose using tear and retinal biomarkers to mirror changes in the brain. The eyes and the brain are closely connected through the optic nerve and both the retina and the central nervous system share a common origin from the developing neural tube. Given this relation, many brain diseases have ocular manifestations [9].

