## Discussion

As the number of people affected by Alzheimer’s disease will grow in the upcoming years due to increased life expectancy, there is a need for an accurate, low-invasive and low-cost diagnostic test that could enable early diagnosis. Future therapies combined with earlier diagnosis can increase the chance for preserving cognitive functioning. When people with cognitive complaints are referred to a memory clinic, a biomarker test (PET scan or CSF puncture) is not always chosen, often due to the fact that they are expensive, invasive, or not available. Diagnosis with tear fluid could lower the bar to apply biomarker tests, since it is low-cost and less invasive. Additionally, tear fluid can be collected at the general practitioner where the patient presents first, enabling timely detection. Tear fluid collection also has the potential to be used for screening purposes, due to its minimally invasive nature.

One of the main strengths of our study is the wide range of information that will be available from the participants, ranging from neuropsychological to ophthalmic tests, which will thereby generate a deeply phenotyped cohort. Furthermore, this study combines measurements of tear and retinal biomarkers, which are both low-invasive methods that potentially complement each other. Potential limitations of our study are that participants may be lost for follow-up visits, due to declining to participate, emigration or study drop-out. Particularly patients with fast cognitive decline may be lost somewhere along the two year follow-up. Another limitation is that not all measurements and data will be available for all participants due to different standard procedures and available equipment per study location.

The TearAD study will be the first longitudinal study analyzing tear AD biomarkers in a large cohort. The first results of the TearAD study, expected by early 2025, will inform whether tear AD biomarkers have added value in the screening and diagnosis of AD.

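### Early detection and screening are the stated purpose, but the accuracy analyses are defined only over a full sample that includes 50 AD dementia patients, with no estimate named for people without dementia

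*Protocol article*

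**What the plan says.** **Purpose.** The Background calls for "tools allowing identification of patients in the earlier phases of the disease". The Discussion says "there is a need for an accurate, low-invasive and low-cost diagnostic test that could enable early diagnosis", adds collection at the general practitioner and possible use in screening, and states that the first results will inform whether tear markers add value for screening and diagnosing AD.

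**Population.** Study population plans 50 participants each with SCD, MCI and AD dementia, plus 50 controls. The resulting 200 are to form 100 with and 100 without neurodegeneration, and no diagnosis is left out of that split.

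**Accuracy analyses.** Statistical analysis sets the ROC contrast as "to differentiate between individuals with neurodegeneration and those without neurodegeneration as determined by hippocampal atrophy". AUC, sensitivity, specificity, predictive values and likelihood ratios follow, with 95% confidence intervals. Accuracy is also planned for tear plus retinal markers combined, with no narrower population given. The post hoc comparisons between groups belong to the models of change over time.

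**Diagnosis subgroups.** Sample size says participants will be divided by clinical diagnosis within the groups, and continues: "We aim to include a 50 participants per clinical diagnosis in order to obtain sufficient data to study secondary outcomes". No accuracy analysis is attached to those subgroups.

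**The concern.** The people for whom an early or screening test is proposed do not yet have a dementia diagnosis. The accuracy figures come from a sample in which one participant in four does.

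Atrophy can be expected to be more frequent in dementia than in controls. Dementia patients would then make up a larger share of the atrophy group than of the group without atrophy. Any marker that differs in dementia separates the two groups to some degree, even if it is unrelated to atrophy within every diagnosis and unchanged in controls, SCD and MCI.

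The pooled figure therefore cannot tell apart a marker that tracks neurodegeneration before dementia and one that registers only established dementia. What is at stake is the conclusion announced in the Discussion, not the validity of the primary estimate.

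**Working it through.** **1. The plan's own sample size.** The target is a 10-point margin, using "an expected proportion (sensitivity and specificity) of 50% was used as this yields the largest sample size".

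n = 1.96² × 0.5 × 0.5 / 0.10² = 96.04, rounded up to 97 per group. The plan's 97 and 97 (194, raised to 200) reproduce. This precision applies to the pooled contrast.

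**2. Inputs for the check.**
- From the article: 50 per diagnosis, 100 with and 100 without atrophy, significance at p < 0.05 (taken as two-sided; the side is not stated).
- Assumed, because the article gives neither: the atrophy rate in each diagnosis, and the size of the marker's shift in dementia.

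**3. Pooled AUC of a dementia-only marker.** Let the marker be normal with SD 1, shifted by d in all dementia patients and in nobody else. Let f1 and f0 be the dementia shares of the groups with and without atrophy, and A = Φ(d/√2). Then

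pooled AUC = 0.5 + (f1 − f0)(A − 0.5).

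A is 0.760, 0.856 and 0.921 for d = 1, 1.5 and 2. Among participants without dementia the AUC is 0.50 by construction.

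- *Steeper rates, 20/30/60/90%* in controls/SCD/MCI/dementia: atrophy counts 10 + 15 + 30 + 45 = 100, so f1 = 0.45, f0 = 0.05 and the difference is 0.40.
- *Flatter rates, 30/40/55/75%*: 15 + 20 + 27.5 + 37.5 = 100, so f1 = 0.375, f0 = 0.125 and the difference is 0.25.
- *Dementia equally common in both groups* (25 of 50 with atrophy): the difference is 0.

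| Assumed rates | d = 1 | d = 1.5 | d = 2 |
|---|---|---|---|
| Steeper: pooled AUC | 0.604 | 0.642 | 0.669 |
| Steeper: share of trials significant | 74% | 96% | over 99% |
| Flatter: pooled AUC | 0.565 | 0.589 | 0.605 |
| Flatter: share of trials significant | about 37% | about 61% | about 81% |
| Equal: pooled AUC | 0.50 | 0.50 | 0.50 |

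The significance rates are from simulated trials of 100 versus 100 with a Mann-Whitney test. For the flatter rates, a repeat with the dementia counts held at 37 or 38 with atrophy gave 34%, 60% and 80%. With the dementia patients removed, simulated trials with 25 to 50 of the 50 dementia patients having atrophy were significant about 5% of the time, as chance alone would give.

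**4. What the other planned measures would show.** Under the steeper rates, at the cutoff that maximises sensitivity plus specificity, the same marker has pooled sensitivity/specificity of 48/67%, 47/75% and 47/81% for d = 1, 1.5 and 2. The positive likelihood ratio is 1.5 to 2.4.

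**5. Precision without dementia.** If 40 to 50 of the 50 dementia patients have atrophy, then 60 to 50 of the other 150 have it and 90 to 100 do not.
- Sensitivity margin: 1.96 × √(0.25/60) = 12.7 points to 1.96 × √(0.25/50) = 13.9 points.
- Specificity margin: 1.96 × √(0.25/90) = 10.3 points to 1.96 × √(0.25/100) = 9.8 points.

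**The case against.** **The ROC fits the objective.** The primary objective, the first outcome measure, the sample size and the ROC all concern atrophy yes or no. This stands: the pooled ROC is a correct primary analysis, and the mismatch is only with the use described in the Background and Discussion.

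**An ROC by stage may be in a document not shown.** It may, and its absence from an article would not be a finding on its own. What remains is that the article states the population, the contrast and the conclusion the results are to inform, and the early-detection part of that conclusion does not follow from that contrast alone.

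**The text is not exclusive.** A reader might infer that a single tear ROC will be run, or that the diagnosis subgroups are barred from accuracy analyses. The article supports neither. It speaks of ROC analyses in the plural, plans accuracy for tear plus retinal markers as well, and foresees division by diagnosis within the groups. It simply attaches no accuracy estimate to that division.

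**A significant AUC is not the study's criterion.** The sample size rests on interval width, and several accuracy measures are reported. A dementia-only marker would show pooled sensitivity below 50%, which already argues against screening use. This limits the harm. It would still not show at which stage the signal arises.

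**The pilot evidence is mixed.** A reader might infer that the tear markers probably change only in dementia. The Background does report higher t-tau in AD dementia than in SCD. It also reports p-tau detected in SCD and MCI but not in controls, and, from another group, lower Aβ42 already in MCI. An early signal is possible, which is a reason to estimate it separately.

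**The claims are hedged.** Most are worded as potential. The sentence on what the first results will inform is firmer, but it covers diagnosis as well as screening.

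**Conclusion.** The concern holds in a limited form. The named accuracy analyses, tear alone and tear plus retinal, pool all diagnoses, and none gives an estimate before dementia. A pooled AUC above 0.5 is therefore compatible with no discrimination at all among people without dementia.

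The size depends on how far dementia is concentrated in the atrophy group and on the shift in dementia, both assumed here. For shifts of 1 to 2 SD, the steeper rates give a pooled AUC of 0.60 to 0.67 (significant in about 74% to over 99% of trials) and the flatter rates 0.57 to 0.61 (about 37% to 81%). There is no effect if dementia is equally common in both groups.

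This is a possibility that the planned figure cannot rule out, not a prediction about these markers. The primary analysis and its sample size stand. The early-detection and screening statement is what lacks a supporting estimate.

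**What to change.** - **Statistical analysis:** keep the pooled ROC as primary. Add a supporting analysis with the same accuracy measures and 95% confidence intervals in the roughly 150 participants without dementia, for tear markers alone and for the tear-plus-retinal combination.
- **Discussion:** state that any early-detection or screening statement rests on the supporting analysis and will not be drawn from the pooled figure alone.
- **Sample size:** give the expected precision of the supporting analysis, with its assumption on how many participants without dementia have atrophy.

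**Cost.** No new data are needed, only a rerun of a planned analysis. Precision is lower: a sensitivity margin of about 13 to 14 points if 50 to 60 participants without dementia have atrophy, against the 10-point target, with specificity staying at about 10 points. If part of the pooled signal comes from dementia, the AUC in this group will also be lower.

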### Study design and setting

This study is an observational longitudinal multicenter study that will be performed at the Maastricht University Medical Center (Maastricht UMC+) and the Amsterdam University Medical Center (Amsterdam UMC) in the Netherlands.

At Maastricht UMC+, people with cognitive complaints who are referred to the memory clinic are asked to participate in ongoing research. If they agreed on being contacted for clinical studies and have the diagnosis SCD, MCI or dementia due to AD they are asked to participate in the present TearAD study. In addition, community-based cognitively healthy controls were recruited through advertisement as part of the GlyM study and later asked to participate in the TearAD study (NL72269.068.19, Glymphatic dysfunction in cognitive impairment: a memory clinic study). Overlapping study procedures will not be repeated, but data will be shared between both studies for which permission granted through the study protocol and informed consent.

At Amsterdam UMC, people with cognitive complaints and a diagnosis of SCD, MCI or AD dementia will be included in the MHIRA study (NL70896.029.19, The diagnostic value of metabolic hyperspectral imaging of the retina in Alzheimer’s disease). These participants originate from the memory clinic based Amsterdam Dementia Cohort [19, 20]. Cognitively healthy controls will be recruited from the Innovative Medicine Initiative European Medical Information Framework for AD (EMIF-AD) PreclinAD study [21]. Agreements on sharing material and data are covered by a material and data transfer agreement between both parties.

Participants for the TearAD study are included from different cohorts with similar study procedures, but different primary endpoints and available infrastructure. For instance, amyloid PET imaging is available in Amsterdam UMC but not in Maastricht UMC+. For this reason, some of our secondary outcome measures will be analyzed in a sub-cohort of the total study population.

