### Study population

Based on their clinical diagnosis we aim to include 50 patients with SCD, 50 patients with MCI and 50 patients with AD dementia. Additionally, 50 cognitively healthy controls will be included. Eventually, the total study population (*n* = 200) will consist of two groups of 100 participants with signs of neurodegeneration and 100 participants without signs of neurodegeneration. The presence of neurodegeneration will be defined as presence of medial temporal lobe atrophy (MTA) (measured by MRI using visual rating scores of the medial temporal lobes using the Scheltens Visual Rating Method abnormal cutoff of ≥ 2 [22]). The inclusion criteria are described in Tables 1 and 2.

**Table 1 Tab1:** Inclusion criteria for all participants

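### PPV and NPV calculated from this quota sample would reflect the recruitment mix, not predictive values for a memory clinic, general practice or screening

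*Protocol article*

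**What the plan says.** The Statistical analysis section says that, alongside the area under the ROC curve, "diagnostic accuracy measures such as sensitivity, specificity, predictive values and likelihood rations (with the corresponding 95% confidence intervals) will be calculated". Their stated purpose is to judge how well a biomarker discriminates. No external prevalence, reweighting or label restricting the predictive values to this sample is given.

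The sample is described under Study population: "we aim to include 50 patients with SCD, 50 patients with MCI and 50 patients with AD dementia", and in addition "50 cognitively healthy controls will be included". The 200 are then expected to consist of "two groups of 100 participants with signs of neurodegeneration and 100 participants without signs of neurodegeneration". Study design and setting shows that this is not one consecutive series. Patients come from two memory clinics. At the Maastricht site, "community-based cognitively healthy controls were recruited through advertisement as part of the GlyM study"; at the Amsterdam site, controls come from a separate preclinical cohort.

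The Sample size section requires that "97 individuals with neurodegeneration and 97 without neurodegeneration will be required", on the basis of precision for sensitivity and specificity only.

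The abstract and the Discussion point the results towards both screening and diagnosis. The Discussion adds that "tear fluid can be collected at the general practitioner where the patient presents first, enabling timely detection". Its limitations cover loss to follow-up and measurements missing at some sites, not the composition of the sample.

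**The concern.** Sensitivity, specificity and likelihood ratios condition on true status. PPV and NPV condition on the test result, so they also depend on the share of people tested who have the target condition. In this study that share comes from how many people of each diagnosis were sought and how many controls were added. No clinic or practice sees one quarter healthy volunteers, one quarter SCD, one quarter MCI and one quarter AD dementia.

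The plan lists predictive values among measures of discrimination without separating the two kinds of quantity. A reader could take a PPV with a 95% confidence interval as the chance that a person with a positive tear test has neurodegeneration in the settings the article names. The interval would reflect sampling error only, and would give no warning that the figure belongs to a different mix of people.

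**Working it through.** **Inputs from the protocol article**

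- Expected share with neurodegeneration: 100/200 = 50% (Study population). The Sample size section implies the same: 97/194 = 50%.
- Healthy controls: 50/200 = 25% of the sample (Study population).
- Planned precision: 95% confidence, half-width 0.10, expected proportion 0.50 (Sample size).

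**Assumed inputs**

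- Sensitivity (Se) and specificity (Sp) of 0.80, with 0.70 and 0.90 as variants. The article gives only the conservative 50% used for sizing.
- Prevalence p in the target setting from 5% to 70%. The article gives none.

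**Step 1: the plan's own figure**

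n = 1.96² × 0.5 × 0.5 / 0.10² = 96.04, rounded up to 97 per group. The stated figure reproduces and is not in dispute.

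**Step 2: predictive values by prevalence**

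PPV = Se·p / [Se·p + (1 − Sp)(1 − p)]

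NPV = Sp(1 − p) / [Sp(1 − p) + (1 − Se)p]

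With Se = Sp = 0.80:

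| Prevalence | PPV | NPV |
|---|---|---|
| 50% (expected in the sample) | 0.40/(0.40 + 0.10) = 80.0% | 0.40/(0.40 + 0.10) = 80.0% |
| 30% | 0.24/(0.24 + 0.14) = 63.2% | 0.56/(0.56 + 0.06) = 90.3% |
| 10% | 0.08/(0.08 + 0.18) = 30.8% | 0.72/(0.72 + 0.02) = 97.3% |
| 5% | 0.04/(0.04 + 0.19) = 17.4% | 0.76/(0.76 + 0.01) = 98.7% |
| 70% | 0.56/(0.56 + 0.06) = 90.3% | 0.24/(0.24 + 0.14) = 63.2% |

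The positive likelihood ratio is 0.80/0.20 = 4.0 in every row.

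**Step 3: other accuracy levels**

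With Se = Sp = 0.70, PPV is 70.0% at 50% prevalence and 20.6% at 10%. With Se = Sp = 0.90, it is 90.0% and 50.0%. The pattern does not depend on the choice of 0.80.

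**Step 4: what the confidence interval would show**

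With 100 per group and Se = Sp = 0.80, there are 80 true and 20 false positives, so 100 test positives. The sample PPV is 80%, with a Wald half-width of 1.96 × √(0.80 × 0.20/100) = 0.078, or about 72% to 88%. That interval contains none of the PPVs in the other four rows.

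**The case against.** The strongest reply is that the article says only that predictive values will be calculated. It does not say that they come straight from the two-by-two table, and a fuller plan could give a prevalence. That is right: direct calculation is an inference. Still, the article groups predictive values with measures of discrimination, attaches confidence intervals and gives no prevalence. Carried out as written, this yields the sample values.

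A second reply also has force. The same sentence plans likelihood ratios, from which a reader can work out predictive values at any prevalence. This softens the problem, but leaves the reported PPV and NPV open to misreading.

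Several stronger readings are tempting, and the document does not support them:

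- **That prevalence is fixed at exactly 50%.** Recruitment is by clinical diagnosis. The even split is an expected composition, and no mechanism is described to enforce it. The realised share may differ, but it would still come from the diagnostic quotas and the added controls.
- **That PPV will be too high and NPV too low.** This holds only where the target prevalence is below the sample's. A memory clinic could lie above it, and the direction then reverses.
- **That the conclusions rest on predictive values.** Nothing says so. The study is sized on sensitivity and specificity, AUC and likelihood ratios are also planned, and the remarks on general practice and screening are Discussion statements about potential use.
- **That raw values must not be reported.** That is a preference. Clearly labelled, they mislead nobody.

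**Conclusion.** The point stands in limited form. PPV and NPV calculated from this sample describe a mix created by diagnostic quotas and separately recruited controls. They do not estimate predictive values for a memory clinic, general practice or screening. At an assumed sensitivity and specificity of 80%, PPV moves from 80% at the expected sample share to between 17% and 63% at prevalences of 5% to 30%, and NPV from 80% to between 99% and 90%. At 70% prevalence they are 90% and 63%. These sizes rest on assumed accuracy and prevalence, since the article gives neither. The dependence on prevalence follows from the formulas for any informative test.

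The sample-size calculation and the AUC are unaffected. Sensitivity, specificity and likelihood ratios do not depend algebraically on prevalence, although the case mix may still influence them.

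**What to change.** In the Statistical analysis section, separate predictive values from the other accuracy measures and state that:

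1. PPV and NPV will be obtained by Bayes' rule from the estimated sensitivity and specificity (or likelihood ratios), over a range of prevalences stated in advance that covers memory-clinic and general-practice use.
2. Their 95% confidence intervals will come from a suitable method, such as the delta method or a bootstrap.
3. Any predictive values taken directly from the study sample will be labelled as specific to its quota composition.
4. Sensitivity and specificity estimated in this mix of recruited controls and diagnosed patients may not transfer fully to general practice, so the figures for that setting are illustrative.

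This needs no new data and does not alter recruitment or sample size. The cost is a few lines of extra analysis and a less favourable PPV at low prevalence. The prevalence range should be set before the accuracy results are seen.
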